## Analysis Populations

### Modified Intention to Treat (ITT) Population

Defined as the ITT population with the exclusion of the lost-to-follow-up patients before Day 28 for unknown reasons (non informative drop-outs). More specifically, patients withdrawing from the study for reasons 7 will be excluded, while all other withdrawals will be counted as failures (these reasons might be considered potentially correlated with lack of efficacy, i.e. are referred to as informative drop-outs).

### Per Protocol (PP) Population (or Evaluable Population)

Defined as all randomized patients who will be eligible according to the study protocol, received at least 80% of the study medication, will not take other anti-malarial drugs and, in case of the presence of asexual parasite stages on thick or thin blood smears, will have an evaluable PCR analysis.

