# JUSTIFICATION FOR THIS STUDY

The inexorable spread of resistance of the malaria parasite *P. falciparum* to affordable antimalarial drugs such as chloroquine and sulfadoxine-pyrimethamine causes a public health crisis in sub-Saharan Africa. In the absence of a registered and effective malaria vaccine in the foreseeable future, antimalarial chemotherapy has to be improved dramatically to replace the currently used antimalarials. WHO currently advocates the use of artemisinin-based combination chemotherapy with prompt antiparasitic action and mutual protection against parasite resistance for the treatment of malaria [23, 24]. At present, the only fixed-dose combination registered up to international standards is artemether-lumefantrine (Coartem®), but artemether-lumefantrine has a rather complex treatment regimen requiring a total of six doses administered twice daily over three days, and the price is high (USD 2.4 under special agreements between the manufacturer and WHO). Other fixed-dose artemisinin-based combinations are under development (artesunate-amodiaquine, or chlorproguanil-dapsone-artesunate) but their future use might be compromised by existing cross-resistance to currently used antimalarial drugs (chloroquine and sulfadoxine-pyrimethamine). Dihydroartemisinin-piperaquine is a promising alternative, which has been shown very safe in more than 5,000 treated patients and proved to be highly effective in areas of multi-drug resistance. A fixed-dose co-formulation of dihydroartemisinin-piperaquine (Artekin) is currently developed according to international standards as a once daily 3-day regimen, which is likely to improve adherence and to increase effectiveness. It is comparably inexpensive costing approximately 1 USD per adult treatment. If proved to be safe and efficacious, dihydroartemisinin-piperaquine will be an important addition to the currently available treatment options for uncomplicated childhood malaria due to multidrug-resistant *P. falciparum* in Kenya.

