### Subject Withdrawal from Study

During the study, the following conditions are reasons for stopping the study treatment and/or for excluding the patients from further efficacy assessments:

1. Any treatment failure (including early failures);

2. Withdrawal of informed consent;

3. Use of antimalarial drugs (or antibiotics with antimalarial activity) outside of the study protocol;

4. Persistent vomiting of study drugs on day 0 (at least twice the same dose);

5. Failure to complete the study treatment;

6. Investigator’s request for safety reasons (for example, onset of serious adverse events, necessitating study interruption);

7. Lost-to-follow up: patient cannot be located by day 28.

Patients with one or more of the conditions listed above will have to be followed-up for the safety assessment until day 42.

These reasons for premature withdrawing will be referred to Day 28 (primary evaluation time). The reasons for withdrawing between Day 29 and Day 42 will also be recorded in the study CRF.

A protocol violation occurs when an event happens that does not allow for accurate interpretation of response to treatment.

Patients meeting one of the following criteria will be considered protocol violations but will not be withdrawn from follow-up:

- violation of any eligibility criteria;
- PCR unclassifiable results;
- failure to attend a follow-up visit on Days 0-2 and patient cannot be located within 6 hours of scheduled time;
- failure to attend two consecutive follow-up visits from Day 3 to Day 28 (visits from Day 3 to 28 must take place within 24 hours of the scheduled time).

The violations listed above are not valid reasons for withdrawing the patients from follow-up (both efficacy and safety assessments). On the contrary, the investigator must do his/her best to respect the allowed time windows at every visit, even if a violation occurred at a previous visit (i.e. a previous visit did not take place or occurred outside the allowed time window).

The protocol violations listed above will not be taken into account for establishing patient inclusion in the intention-to-treat population while they will be a reason for excluding the patients from the evaluable population.

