#### Dihydroartemisinin-piperaquine (Artekin)

The drug will be given once daily for 3 days.

Dosing schedule

Medications will be administered at the following times:

Day 0: hour “X”

Day 1: hour “X” + 24 hours

Day 2: hour “X” + 48 hours

Dosing table

One tablet of Artekin contains either 20 mg of dihydroartemisinin and 160 mg of piperaquine or 40 mg of dihydroartemisinin and 320 mg of piperaquine. The dosing will be based on bodyweight (assuming a linear relationship between key pharmacokinetic parameters and body weight).

| **Weight in kg** | **mg of dihydroartemisinin to be given daily** | **Dose of dihydroartemisinin as mg/kg/d** |
| --- | --- | --- |
| 4 - 6 | 10 (1/2 tablet with 20 mg) | 1.67 - 2.5 |
| 7 - 12 | 20 (1 tablet with 20 mg) | 1.67 - 2.86 |
| 13 - 23 | 40 (1 tablet with 40 mg) | 1.74 - 3.08 |
| 24 - 35 | 80 (2 tablets with 40 mg) | 2.29 - 3.33 |
| 36 - 75 | 120 (3 tablets with 40 mg) | 1.6 - 3.64 |

| **Weight in kg** | **mg of piperaquine to be given daily** | **Dose of piperaquine as mg/kg/d** |
| --- | --- | --- |
| 4 - 6 | 80 (1/2 tablet with 160 mg) | 13.36 - 20 |
| 7 - 12 | 160 (1 tablet with 160 mg) | 13.36 – 22.88 |
| 13 - 23 | 320 (1 tablet with 320 mg) | 13.92 – 24.64 |
| 24 - 35 | 640 (2 tablets with 320 mg) | 18.32 – 26.4 |
| 36 - 75 | 960 (3 tablets with 320 mg) | 12.8 – 29.12 |

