#### Artemether-lumefantrine (Coartem©)

Artemether-lumefantrine (Coartem®, Norvatis Pharma, Basel Switzerland) is co-formulated as fixed-ratio film tablets containing 20 mg artemether and 120 mg lumefantrine. Dosing will follow the recommendations of the manufacturer.

Dosing schedule

Medications will be administered at the following times:

Day 0: hour “X”

Day 0: hour “X” + 8 hours

Day 1: hour “X” + 24 hours

Day 1: hour “X” + 36 hours

Day 2: hour “X” + 48 hours

- 5 - < 15 kg: 1 tablet per dose
- 15 - < 25 kg: 2 tablets per dose
- 25 - < 35 kg: 3 tablets per dose

Tablets will be given, whenever possible with food/drink ~100 ml of reconstituted full cream milk or breast milk as appropriate. In case the infant/child is not able to ingest tablets, the tablet(s) will be dissolved before administration.

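### The 80% medication rule for the per-protocol population tolerates one missed dose in the comparator arm but none in the test arm, and it does not fit the withdrawal rule for incomplete treatment

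*Protocol*

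**What the plan says.** - **PP membership.** Section 12.2.2 requires, among other things, that the child "received at least 80% of the study medication". It does not say whether the share is counted in doses, tablets or milligrams.
- **Role of PP.** Sections 10.4.2 and 12.3.1 make PP the population for the primary analysis. The lower limit of the one-sided 97.5% interval for the cure difference must lie above -0.05, and the test drug's cure ratio must exceed 90%.
- **Test regimen.** Section 11.1.1.2: "The drug will be given once daily for 3 days".
- **Comparator regimen.** Section 7 describes it as "requiring a total of six doses administered twice daily over three days". Section 11.1.1.3 lists only five administration times, the last being "Day 2: hour “X” + 48 hours".
- **Withdrawal.** Reason 5 in section 10.8.2 is "Failure to complete the study treatment", with no percentage attached. It is one of the "reasons for stopping the study treatment and/or for excluding the patients from further efficacy assessments".
- **Other populations.** For the modified ITT population, section 12.2.1 leaves out only reason 7 (loss to follow-up), "while all other withdrawals will be counted as failures". Section 12.2.3 gives a second condition for being evaluable: parasite counts recorded to day 28, or discontinuation for a PCR-confirmed recrudescence.

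**The concern.** A single percentage looks neutral, but it acts on courses with different numbers of doses. A child who loses one whole dose leaves PP in the test arm and stays in PP in the comparator arm. If losing a dose lowers the chance of cure, the comparator's PP cure ratio falls while the test drug's does not, and the difference moves towards a non-inferiority claim. The trial is open label, and doses are likely to be lost through refusal, vomiting or illness. Section 12.2.1 itself treats such withdrawals as possibly related to lack of efficacy.

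The protocol also gives no single answer for a comparator child with one missed dose. Section 12.2.2 admits the child to PP. Section 10.8.2 may end efficacy assessment, section 12.2.1 counts a withdrawal for this reason as a failure, and section 12.2.3 makes the child non-evaluable if day-28 counts are absent.

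**Working it through.** The protocol gives no figure for this rule, so there is none to reproduce. The check has three parts.

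**1. Share of medication left after one whole missed dose.** With equal doses, share = (doses - 1)/doses, compared with 80%.

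| Arm | Doses | Source | Share left | PP under 12.2.2 |
|---|---|---|---|---|
| Dihydroartemisinin-piperaquine | 3 | 11.1.1.2 | 2/3 = 66.7% | out |
| Artemether-lumefantrine | 6 | section 7 | 5/6 = 83.3% | in |
| Artemether-lumefantrine | 5 | 11.1.1.3 | 4/5 = 80.0% | in (threshold met exactly) |

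Two missed of six leaves 4/6 = 66.7%, which is out. So the rule tolerates no whole missed dose in the test arm and one in the comparator.

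There are two limits. Half a dose lost in the test arm leaves 2.5/3 = 83.3%, and that child stays in, so the asymmetry concerns whole doses. Also, if the denominator is six but only the five listed times are used, a child who misses one of those five has 4/6 = 66.7% and is out. The result therefore depends on reconciling section 7 with section 11.1.1.3.

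**2. The comparator child with one missed dose, under each reading of reason 5.**

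- *Strict reading* (any incomplete course ends efficacy assessment): the child may have no day-28 count and then is not evaluable under 12.2.3. The 80% tolerance has no effect, and the tilt between arms does not arise.
- *Loose reading* (only treatment stops, or reason 5 is taken to mean below 80%): the child keeps a day-28 outcome and counts in PP, while the test-arm child with one missed dose does not. The tilt arises.

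**3. Size under the loose reading.** Assumptions, none from the protocol: a share m of children in each arm misses exactly one dose and is cured at ratio c. Fully dosed children are cured at 95%, the comparator figure in 10.4.2. Test-arm children with a missed dose are removed and comparator ones are kept.

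Shift in the PP difference = m × (0.95 - c):

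- m = 2%, c = 0.90: 0.02 × 0.05 = 0.1 points
- m = 2%, c = 0.80: 0.02 × 0.15 = 0.3 points
- m = 5%, c = 0.80: 0.05 × 0.15 = 0.75 points
- m = 5%, c = 0.70: 0.05 × 0.25 = 1.25 points

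With 250 comparator children, 0.3 points is 0.75 of a child and 1.25 points is about 3 children.

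Effect on the error rate of the non-inferiority criterion alone: take the protocol's 235 per arm as given and a true difference at the margin (90% against 95%). The standard error is √[(0.90 × 0.10 + 0.95 × 0.05)/235] = 0.0242. The false-claim probability is 1 - Φ(1.96 - shift/0.0242). It rises from 2.5% to about 2.8%, 3.3%, 4.9% and 7.4% for the four shifts above.

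**The case against.** Much of the problem is already covered. Section 10.8.2 treats as a protocol violation, in both arms, a missed visit on days 0 to 2 when the child cannot be found within 6 hours, and it excludes such children from the evaluable population. Repeated vomiting of the same dose on day 0, safety stops and withdrawn consent are withdrawal reasons in both arms. Intake is observed, at home if necessary, and section 11.1.1.1 provides for re-dosing after vomiting. What remains is mainly located children who lose one whole dose through refusal or through vomiting after day 0. Evening doses given at home may be added if those contacts do not count as follow-up visits. This objection stands, and it makes 5% missing exactly one dose a high assumption.

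The ITT and modified ITT analyses count reason-5 withdrawals as failures in both arms alike. That is a useful cross-check, but it does not repair the primary population.

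A reader might infer more than the text supports:

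- That the tilt and the lost day-28 outcomes add up. They do not; they belong to alternative readings of reason 5.
- That efficacy follow-up necessarily stops. The wording is and/or, so the text permits this without requiring it.
- That every test-arm child must be fully dosed to be evaluable. The half-dose case shows otherwise.

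**Conclusion.** The point holds in limited form. As written, section 12.2.2 treats one whole missed dose differently in the two arms of the primary population, and it does not fit reason 5 of section 10.8.2. This follows from the protocol's own dose counts and needs no assumption beyond equal doses and one consistent comparator total.

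The size does need assumptions. It is about 0.1 to 1.25 points of the 5-point margin, and zero if reason 5 is applied strictly. It is probably near the low end, because dosing is observed and missed visits are already handled. A reader might take a quarter of the margin (1.25/5) as the expected bias. It is the extreme of the assumed range and takes no account of the existing exclusions.

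The effect concerns the non-inferiority criterion. The 90% criterion is not shifted, because test-arm children with a whole missed dose are out of PP under the present rule and would also be out under a rule requiring every dose. The change is worth making because the rule defines the primary population, any tilt would probably favour the claim, and the repair is short.

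**What to change.** 1. First reconcile section 7 (six doses) with section 11.1.1.3 (five listed times), so that the scheduled course is defined for the comparator.
2. In 12.2.2, replace the percentage with an adherence rule that acts equally in both arms. One example is all scheduled doses received, with a dose repeated under 11.1.1.1 counting as received. State how a partly taken dose is classed, identically for both arms.
3. In 10.8.2, state that children with incomplete treatment keep their scheduled slides to day 28, and that the PP definition alone decides whether they are excluded from PP.
4. Align 10.8.2, 12.2.2 and the evaluability condition in 12.2.3, so that one child has one status.
5. Report exclusions for incomplete dosing by arm.

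Apart from the reconciliation, the cost is about one sentence each in 12.2.2 and 10.8.2, plus consistent wording in 12.2.3. The downside is that a few more comparator children leave PP. The comparator has more doses to miss, so exclusions may still differ in number between arms, which is why item 5 is needed.

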### Safety population

All subjects who have received any dose of the study medication will be included in the safety population. The analysis of the 28 and 63-day cure ratios will be performed both for the intention-to-treat (ITT) patient population (all randomised patients) and the evaluable patient population. Patients are evaluable for the analysis of the 28 and 63-day cure ratios if parasite counts are recorded up to Day 28 and 63 or the patient discontinues due to reappearance of *P. falciparum* confirmed by PCR genotyping to be recrudescent.

The ITT analysis also includes patients who discontinue before Days 28 and 63 due to other reasons. These patients will be counted in the ITT analysis as treatment failures regardless of their reason for discontinuation.

Safety and tolerability measurements will be summarised for the ITT patient population.

## Statistical Analysis

### Primary end point analysis

The primary analysis will be based on a 97.5% (one-sided) confidence interval (CI) computed on the difference between the 28-day PCR corrected cure ratios (PP population) of the test and the reference treatments, respectively.

In order to claim that dihydroartemisinin-piperaquine is efficacious, the lower limit of the 97.5% confidence interval of the difference between the treatment groups must be >-0.05 and the point estimate for the 28-day PCR corrected cure ratio of dihydroartemisinin-piperaquine must be >0.90%, in the PP population.

All patients withdrawn from the study will be considered as failures in the ITT population (worst-case scenario).

For computing the PCR-corrected cure ratio, the following rules will be applied:

- The patients with reappearing asexual parasitaemia, which are subsequently found to be due to re-infections are considered as treatment success in both PP and ITT populations;
- The patients for whom the PCR analysis is not interpretable (or blood sample unavailable) are considered as treatment failure in the ITT population, but are excluded from the PP population.

Robustness of results for the primary end point will be investigated by using other analyses, such as the survival analysis techniques.

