# ABSTRACT

Artekin is an artemisinin-based fixed-dose antimalarial drug combination developed in the 1990s in China. The active components are dihydroartemisinin and piperaquine. Piperaquine is a bisquinoline compound originally synthesized in France with high *in vitro* activity in the nanomolar range against multidrug resistant *Plasmodium falciparum*. Piperaquine has been used as monotherapy in China for over two decades. It has proved to be generally very well tolerated and effective although resistance to the monotherapy has developed until the early 1990s prompting its reformulation in combination with other drugs, including dihydroartemisinin. Dihydroartemisinin has already been extensively evaluated and shown to be safe – with no major identifiable adverse effects. The combination has become widely used in South East Asia and is now registered in Cambodia, China and Vietnam.

Several factors make this combination a promising development: Artekin is a fixed-dose co-formulation used as a once daily 3-day regimen, and this may improve adherence and ease of drug administration in comparison for instance to the more complex regimens of artemether-lumefantrine (Coartem©). It is also inexpensive in comparison with other artemisinin-based combination chemotherapies, e.g. Coartem© or artesunate-mefloquine with an estimated cost per adult treatment of approximately 1 USD. Finally, preliminary clinical trials of this treatment in more than 5,000 patients carried out in South East Asia have shown it to be well tolerated and highly effective on par with Coartem© and artesunate-mefloquine in areas of high-level multi-drug resistance of *P. falciparum*.

This study is part of a multicentre phase III trial aimed at evaluating the safety and efficacy of the newly manufactured GMP batch of Artekin in 1,500 African children with uncomplicated *P. falciparum* malaria. In Kilifi, 500 patients aged 6-59 months with uncomplicated *P. falciparum* malaria will be randomly allocated to receive either dihydroartemisinin-piperaquine or artemether-lumefantrine. The objective of the study is to evaluate the efficacy and safety of dihydroartemisinin-piperaquine and to demonstrate that dihydroartemisinin-piperaquine (1) is at least as effective as artemether-lumefantrine and (2) cures at least 90% of treated patients.

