Dihydroartemisinin-piperaquine is co-formulated as a film tablet containing 40 mg of dihydroartemisinin and 320 mg of piperaquine phosphate for oral treatment of uncomplicated *P. falciparum* malaria. Dose finding studies in Thailand and Vietnam established the excellent safety and high efficacy of a once daily 3-day regimen of dihydroartemisinin at 4 mg/kg/day [21]. These phase II-type studies were conducted with the currently available non-GMP formulation in the expectation that oral bioavailability of the new GMP formulation will be similar. We will use the new GMP formulation provided by SigmaTau (Italy) in this study. Our study will be part of a phase III multicentre trial involving five studies sites in five African countries.

Piperaquine has a long terminal elimination half-life of approximately 14 days [11]. This might favour an accelerated emergence and spread of resistant parasite alleles, but by acting as a selective filter at time of reinfection [22].

Dihydroartemisinin-piperaquine is an ACT that seems to offer a highly efficacious, safe, well tolerated, simple and affordable treatment option for uncomplicated *P. falciparum* malaria in endemic countries.

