## Outcome measures and sample size.

### End points

#### Primary end point

The primary end point will be the PCR-corrected adequate clinical and parasitological response (PCR corrected ACPR) at day 28.

ACPR is defined as the absence of parasitaemia on day 28 irrespective of the axillary temperature without previously meeting any of the criteria of early treatment failure or late clinical or parasitological failure.

Patients with late asexual parasite reappearance will be considered ACPR if the PCR analysis shows a new infection rather than a recrudescence.

The total treatment failure is defined according to the WHO criteria [25] as the sum of early and late treatment failures (for definitions see chapter 7.3 Treatment failure).

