#### Secondary end points

The secondary end points will be:

1. Crude (PCR uncorrected) adequate clinical and parasitological response ratio at day 28 (PCR-uncorrected ACPR)
2. Cure ratios at days 42, 63, and 84 (PCR-corrected and PCR-uncorrected ACPR)
3. Fever clearance time (FCT)

Fever clearance time will be defined as the time (in hours) from the start of a patient’s treatment to the first consecutive axillary temperature measurements below 37.5°C (body temperature <37.5ºC for at least 48 hours).

1. Asexual parasite clearance time (PCT)

Asexual parasite clearance time will be defined as the time (in days) from the start of a patient’s treatment to 2 consecutive negative blood slides (collected at different days).

1. Gametocyte carrier rates and geometric mean densities (excluding negatives) will be compared on days 7, 14, 28 and 42.
2. Changes of haemoglobin (Hb) concentration from day 0 to days 28, 42, 63, and 84.
3. Safety profiles of the two treatments.
4. Adverse events, vital signs, blood chemistry and haematology, electrocardiogram (ECG) will be monitored and changes in relevant laboratory parameters will be assessed.
5. Rate of PCR-confirmed reinfections
6. Plasma concentration of piperaquine at time of asexual parasite reappearance.
7. Detection of subpatent asexual parasitaemia on day 7 **and day 14**
8. **Assessment of the relationship between *var* gene transcription patterns and late asexual parasite recurrence**

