### Secondary end point analyses

#### Secondary efficacy end point analyses

Normally distributed variables will be summarized by calculating means and standard deviations (SD) and compared with parametric tests (unpaired and paired Student’s *t* or analysis-of-variance (ANOVA) tests as appropriate). Non-normally distributed variables will be summarized by median and interquartile ranges (IQR) or geometric means and 95% confidence intervals. Comparisons will be made with nonparametric tests (unpaired and paired Wilcoxon or Kruskal-Wallis rank tests as appropriate). The Fisher’s exact test will be used to assess differences in categorical outcome variables between the cohorts. The statistical significance level will be set to 5%.

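### PCR-corrected cure at days 42, 63 and 84 is covered only by Fisher's test for a difference, so follow-up past two piperaquine half-lives cannot show whether day 28 non-inferiority persists

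*Protocol*

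**What the plan says.** Section 10.4.1.1 sets the time point: "The primary end point will be the PCR-corrected adequate clinical and parasitological response (PCR corrected ACPR) at day 28". Section 12.3.1 attaches the decision to it: "The primary analysis will be based on a 97.5% (one-sided) confidence interval (CI) computed on the difference between the 28-day PCR corrected cure ratios". The efficacy claim needs a lower limit above -5 points and a test-arm point estimate above 90%, both in the per-protocol population.

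Section 6 says "Piperaquine has a long terminal elimination half-life of approximately 14 days". On dosing, 11.1.1.2 says "The drug will be given once daily for 3 days", so the last dose is on day 2. Sections 9.2 and 10.2 expect a chemoprophylactic effect and plan to estimate it.

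Follow-up runs to day 84, and 10.4.1.2 lists "Cure ratios at days 42, 63, and 84 (PCR-corrected and PCR-uncorrected ACPR") as secondary end points. Section 12.2.3 adds populations for one of the later days: "The analysis of the 28 and 63-day cure ratios will be performed both for the intention-to-treat (ITT) patient population", and also for the evaluable population. It names no method. The method comes from the general rule in 12.3.2.1, where Fisher's "exact test will be used to assess differences in categorical outcome variables between the cohorts", at a 5% significance level. No margin or confidence interval for the difference is given there. Survival techniques appear in 12.3.1 only as a robustness check on the primary end point.

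Sections 8 and 9.1 tie hypothesis and objective to day 28. The abstract (section 5) states the aim without a day: the drug is to be shown at least as effective and to be one that "cures at least 90% of treated patients".

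**The concern.** PCR correction separates reinfection from recrudescence among parasites that have reappeared. It cannot count a recrudescence that has not yet surfaced. If residual piperaquine delays some recrudescences beyond day 28, the day 28 ratio in the test arm is higher than the cure eventually achieved.

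The trial collects the data to examine this: PCR-corrected cure to day 84, when far less drug remains. But the stated test changes the question. At day 28 the plan asks whether the test drug is worse by 5 points or more. At the later days it asks whether any difference is significant at 5%. A non-significant answer to the second question says nothing definite about the first. A reader who wants to know whether the day 28 result persists would get a p-value that cannot tell them.

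**Working it through.** **Inputs.** Half-life 14 days (section 6); doses on days 0 to 2 (11.1.1.2); margin 5 points, reference cure 95%, 235 evaluable per group (10.4.2); decision rule (12.3.1). The interval method is not stated, so a Wald interval is assumed. Final cure ratios other than 95%, and the share of failures delayed past day 28, are assumptions.

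**The plan's own figure.** n = (z_alpha + z_beta)² × 2p(1-p) / margin², with p = 0.95 and 80% power, gives (1.960 + 0.842)² × 0.095 / 0.0025 = 299 per group at the stated one-sided 0.025. The stated 235 is reproduced only at one-sided 0.05. That is a separate matter; 235 is used below because it is the planned number.

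**1. Residual drug.** Fraction = 0.5^(t/14), a simple extrapolation of the terminal half-life.
- Day 28 from first dose: 28/14 = 2.0 half-lives, 25%. From last dose: 26/14 = 1.86, 28%.
- From first dose: day 42, 12.5%; day 63, 4.4%; day 84, 1.6%.

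**2. What Fisher's test can detect.** Exact power, two-sided 5%, 235 per arm, reference 95%:

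| Test-arm cure | Power |
| --- | --- |
| 92% | 21% |
| 90% | 48% |
| 88% | 74% |
| 86% | 90% |

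A true deficit equal to the margin (90% v 95%) is therefore missed 52% of the time.

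**3. Example.** Test 212/235 = 90.2%, reference 223/235 = 94.9%, difference -4.7 points.
- Fisher's p = 0.078, not significant.
- SE = sqrt(0.902 × 0.098/235 + 0.949 × 0.051/235) = 0.0241. Lower limit = -0.0468 - 1.96 × 0.0241 = -0.094, or -9.4 points, well beyond -5.

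The same data are not significant on one method and clearly fail to show non-inferiority on the other.

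**4. How far delay could matter at day 28.** Assume final cure of 90% test and 95% reference. The chance of meeting the 12.3.1 rule is found by exact binomial enumeration at 235 per arm. Day 28 cure = 1 - (1 - final cure) × (1 - share delayed).

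| Share of failures delayed | Test arm only | Both arms equally |
| --- | --- | --- |
| None | 3% (90% v 95%) | 3% (90% v 95%) |
| A quarter | 22% (92.5% v 95%) | 10% (92.5% v 96.25%) |
| Half | 71% (95% v 95%) | 33% (95% v 97.5%) |

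Brackets show day 28 cure, test v reference. The result depends heavily on two quantities that the documents do not give.

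**The case against.** **Day 28 is openly chosen and kept throughout.** Sections 8, 9.1, 10.4.1.1, 10.4.2 and 12.3.1 agree on it, and 10.2 keeps the data compatible with the multicentre protocol. Late failures are collected and reported, not hidden. This stands, and is why day 28 should remain the primary decision. Only the abstract leaves the day out.

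**Section 12.3.2.1 is a generic sentence and an analysis plan could add intervals.** It does not name the later cure ratios. But they are categorical secondary efficacy outcomes, no other stated rule covers them, and the method that is stated does not suit a non-inferiority trial. The protocol does not say that a non-significant result will be read as equivalence; the point is that it could not support that reading.

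**Fisher's test is not empty.** A significant result against the test drug would contradict the day 28 claim, with 90% power at 86% v 95%. This stands. A reader might infer that the later comparisons can neither support nor overturn day 28; only the first half is true.

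**The day 28 comparison need not favour the test drug.** A reader might infer from the 22% and 71% that suppressed failures will pass as non-inferior. Those figures assume that no reference failure is delayed. With equal delay they fall to 10% and 33%. The protocol gives no lumefantrine half-life and no delayed share for either arm, so the net bias between arms cannot be sized.

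**Later days are not clean.** At day 42 an estimated 12.5% of the drug remains, so it is less suppressed, not free of suppression. Reinfections also count as successes and accumulate with follow-up.

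**Conclusion.** The point holds in a limited form. The efficacy claim rests on a day about two piperaquine half-lives after dosing, and the only method stated for the later cure ratios cannot show whether non-inferiority persists. At 235 per arm, Fisher's test misses a 90% v 95% deficit about half the time. That figure rests on the planned number evaluable and an assumed pair of cure ratios. That recrudescences may be delayed is reasonable on the protocol's own half-life, but the extent, and any difference between arms, is unknown.

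A reader might go further and make the efficacy claim conditional on day 42. The documents do not support that: 10.4.2 sets the margin and the 90% floor for day 28. It would make day 42 in effect co-primary. With truly equal arms, the chance of meeting the same rule at day 42 is only 57% at 93% v 93% and 71% at 95% v 95% (exact enumeration, 235 per arm).

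**What to change.** - Keep PCR-corrected cure at day 28 as the sole primary decision.
- In 12.3.2.1, replace Fisher's test for the PCR-corrected cure ratios at days 42, 63 and 84 with the difference (test minus reference) and its one-sided 97.5% confidence interval, whose lower limit equals that of the two-sided 95% interval, in the PP and ITT sets. Show it against the -5 point margin and label it supportive.
- Report the test-arm cure ratio at each of these days with its confidence interval.
- State the primary conclusion as cure to day 28, and add the day to the aim in the abstract.
- Do not make the claim conditional on day 42.

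The later ratios also need a complete failure definition. In 11.3.2.1, parasitaemia with fever counts only to day 28, while 11.3.2.2 runs to day 84 but requires absence of fever. A febrile recrudescence after day 28 without danger signs or severe malaria fits neither, so the two sections should be reconciled.

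The cost is wording and a little more analysis; visits and genotyping are already planned. The downside is that the later intervals may be inconclusive.
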